**Methods:**

We designed a multi-centre randomised controlled trial with a follow-up of 12 months. Patients who have paid employment at the time of diagnosis, are on sick leave and are between 18–62 years old will be eligible to participate. After patients have signed the informed consent form and filled in the baseline questionnaire, they are randomly allocated to either the nurse-led, stepped-care, e-health intervention called Cancer@Work, or care as usual. The primary outcome is sustainable return to work. Secondary outcomes are sick leave days, work ability, work functioning, quality of life, quality of working life and time from initial sick leave to full return to work without extensive need for recovery. The feasibility of the Cancer@Work intervention and direct and indirect costs will be determined. Outcomes will be assessed by questionnaires at 3, 6, 9 and 12 months of follow-up.

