#### Conditions of use

There is no prescribed use of the Cancer@Work intervention in terms of length, frequency or duration. Patients themselves decide when to use the Cancer@Work intervention and which content to use. They will go through the Cancer@Work intervention at their own pace and move from step 1 to step 2 if indicated. The Cancer@Work intervention will be available for 12 months.

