### Assessment of the outcomes

Data will be both self-reported and collected by recording use of the Cancer@Work intervention by participants and recording the content of the assignments made by participants. The self-reported outcomes will be assessed at baseline and at 3, 6, 9 and 12 months of follow-up using questionnaires that will be completed by participants randomised to the intervention group and control group with online software. All participants will receive an email with a link to complete the questionnaire online if they indicate to prefer questionnaires online; otherwise, they will receive paper questionnaires. Completing a questionnaire will take approximately 30 minutes.

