#### Prognostic and descriptive characteristics

Prognostic characteristics are age, gender, marital status (married, single, widowed, divorced), bread winner status (yes, no, shared), education (7 categories), cancer diagnosis, treatment type (surgery, radiotherapy, chemotherapy, hormonal therapy, other), time since diagnosis (in months), treatment duration and comorbidity (13 diseases). Work-related factors include characteristics of the job (working hours per week, job position, company size, shift work (no, yes with/without night shifts), type of contract (permanent, temporary, self-employed), years in present position, years of work experience, and work adjustments), work demands (VBBA) [39], importance of work (0 (not important)–100 (most important)), current problems with work (yes/no), need for information or support regarding work-related problems (1 (no)–5 (very much)) and expectations regarding return to work in next 4 weeks (1 (definitely yes)–4 (probably not)). Fatigue is measured with the 20-item Multidimensional Fatigue Inventory (MFI) [40] with higher scores indicating more fatigue, depression is measured with the 20-item CES-D [41] with higher scores indicating more depressive symptoms and cognitive functioning at work is measured with the 20-item Cognitive Symptom Checklist-Work questionnaire [42]. The following descriptive characteristics will be measured: income (in euros per month) and work participation status at follow-up (employed, unemployed, disability pension, retired).

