#### Intermediate effect of the Cancer@Work intervention on self-management and work-related self-efficacy

The Cancer@Work intervention is a self-management intervention based on problem-solving techniques and cognitive behavioural techniques. The key mechanisms of the Cancer@Work intervention are therefore self-management skills and work-related self-efficacy. To measure this change in self-management skills, we will measure perceived confidence in own self-management skills on a visual analogue scale of 0 (no confidence) to 100 (high confidence). Work-related self-efficacy will be measured with the 11-item questionnaire ‘expectations regarding work functioning’ [43] with higher scores indicating more self-efficacy regarding work.

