#### Effectiveness

The relative risk and 95 % confidence interval for returning to work at 12 months of follow-up will be calculated for the intervention group versus the control group. In addition to this ITT analysis aimed at ’all-cause return to work’, the analysis will be performed excluding those patients who have died during follow-up and those who have a life expectancy of less than a few months, because they will not return to work.

To assess whether the Cancer@Work intervention is more effective for those who need it most, a planned subgroup analysis for patients with a high risk of not returning to work will be performed. This subgroup will be identified based on having physical heavy work, low work ability at baseline, high levels of fatigue, depression and cognitive problems at work at 3 and 6 months of follow-up and a long duration of cancer treatment [13, 30]. In addition, to ascertain whether the Cancer@Work intervention is more effective for various subgroups of patients who are more or less prone to benefit from self-management, a subgroup analysis will be done for young versus old, male versus female and lower education level versus higher education level [44].

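### The high-risk subgroup is defined partly by symptoms measured 3 and 6 months after randomisation, so allocation can change who is in it

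*Protocol article*

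**What the plan says.** Under Statistical analysis, Effectiveness, the Protocol article states that "a planned subgroup analysis for patients with a high risk of not returning to work will be performed". Its purpose is to see whether the patients with the greatest need gain more. Membership rests on two kinds of criteria in the same sentence. The first are "having physical heavy work, low work ability at baseline". The second are "high levels of fatigue, depression and cognitive problems at work at 3 and 6 months of follow-up and a long duration of cancer treatment".

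On timing, the abstract says: "After patients have signed the informed consent form and filled in the baseline questionnaire, they are randomly allocated". Conditions of use adds: "The Cancer@Work intervention will be available for 12 months". Assessment of the outcomes says: "The self-reported outcomes will be assessed at baseline and at 3, 6, 9 and 12 months of follow-up". Randomisation, blinding and treatment allocation states that patients, care providers and the researcher all know the allocation.

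On the instruments, Prognostic and descriptive characteristics names the MFI for fatigue and the CES-D for depression, and says that "cognitive functioning at work is measured with the 20-item Cognitive Symptom Checklist-Work questionnaire". It gives no time point for any of the three.

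**The concern.** A subgroup comparison keeps the benefit of randomisation only if membership could not have been influenced by allocation. Here three criteria are recorded 3 and 6 months after allocation. If the intervention changes symptoms, changes how unblinded patients report them, or changes who is back at work or who replies by then, the high-risk patients in one arm are a different kind of patient from those in the other. The subgroup RR then mixes the treatment effect with that difference.

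This is the analysis meant to show whether the intervention helps most where the need is greatest. The commitment to intention-to-treat does not repair it, because patients can be analysed as allocated and still be sorted by something that allocation influenced.

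**Working it through.** **1. Timing.** Randomisation follows the baseline questionnaire, and the intervention is available for 12 months. The 3- and 6-month scores therefore fall after allocation and during exposure. Work ability, in the same sentence, is tied to baseline, so the later timing reads as a choice. If the time point is taken to govern only cognitive problems, that criterion is still post-randomisation. Nothing in the article restores a baseline definition or labels the analysis descriptive.

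**2. Routes by which membership can shift.**
- Symptoms or their reporting: "The Cancer@Work intervention is a self-management intervention based on problem-solving techniques and cognitive behavioural techniques". An effect on fatigue or mood is plausible, and the scores are unblinded self-report.
- Early return: Sample size puts return at about 8% in the first 42 days and assumes 72% for controls by the end of follow-up. Some patients will be back before 3 or 6 months (the article gives no rate at those times), and being at work can affect the scores.
- Cognitive problems at work seem to require working.
- Classification needs a reply at 3 and 6 months, so unequal non-response would add selection.

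**3. The plan's own figure.** The subgroup analysis has none. The trial's sample size, given only as context, reproduces with 72% v 89%, 80% power and two-sided 5% (sidedness is not stated):

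n per arm = [1.960 × √(2 × 0.805 × 0.195) + 0.842 × √(0.72 × 0.28 + 0.89 × 0.11)]² / 0.17² = (1.098 + 0.461)² / 0.0289 ≈ 84.1, so 85 per arm and 170 in total. Then 170 / 0.90 = 188.9, that is 189, or 190 as an even number.

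**4. Illustration of the bias.** None of these assumptions is in the documents.
- Latent risk U ~ N(0,1).
- Return to work has probability 1 / (1 + exp(−(1.13 − U))), about 72% overall, with no treatment effect (true RR 1.00).
- Follow-up symptom score S = ρU + √(1 − ρ²)e − δT, with e ~ N(0,1), T = 1 for intervention, ρ = 0.5 or 0.7, and δ the symptom reduction in SD.
- High risk means the worst third of the control-arm scores. One symptom score stands in for the whole rule.
- 4 million simulated patients per scenario.

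| δ | ρ | In subgroup, intervention v control | Return to work in subgroup, intervention v control | Subgroup RR |
|---|---|---|---|---|
| 0 | 0.5 | 33.2% v 33.3% | 62.2% v 62.3% | 1.00 |
| 0 | 0.7 | 33.3% v 33.3% | 58.0% v 58.0% | 1.00 |
| 0.2 | 0.5 | 26.4% v 33.3% | 60.7% v 62.2% | 0.98 |
| 0.2 | 0.7 | 26.4% v 33.3% | 55.9% v 58.1% | 0.96 |
| 0.3 | 0.5 | 23.2% v 33.3% | 59.9% v 62.2% | 0.96 |
| 0.3 | 0.7 | 23.3% v 33.3% | 54.6% v 58.1% | 0.94 |
| 0.5 | 0.5 | 17.6% v 33.3% | 58.3% v 62.2% | 0.94 |
| 0.5 | 0.7 | 17.6% v 33.3% | 52.3% v 58.0% | 0.90 |

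The whole-sample RR was 1.00 throughout. So was the RR in a subgroup defined by the baseline variable U.

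**5. Hand check.** The share of the intervention arm entering is 1 − Φ(0.431 + δ): 1 − Φ(0.631) = 0.264 at δ = 0.2, and 1 − Φ(0.931) = 0.176 at δ = 0.5. Mean latent risk among members is ρφ(c)/(1 − Φ(c)), where c is the cut-off. With ρ = 0.7 and δ = 0.5 this is 0.7 × 0.364 / 0.333 = 0.76 for controls and 0.7 × 0.259 / 0.176 = 1.03 for intervention. The intervention patients who still qualify are the sicker ones, which is why the RR falls below 1.

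**6. Against sampling error.** With 85 per arm, the most biased row has about 85 × 0.333 = 28 controls and 85 × 0.176 = 15 intervention patients. The SE of log RR is √(0.420/(28 × 0.580) + 0.477/(15 × 0.523)) = 0.29. The bias is ln(0.903) = −0.10, about a third of one SE. The confidence interval would not reflect this bias, and a larger sample would not remove it.

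**The case against.** The best counter-arguments limit the point without removing it.

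- **An effect on symptoms is not claimed.** The article names self-management skills and work-related self-efficacy as the mechanisms, and lists fatigue, depression and cognitive functioning only as prognostic characteristics. If allocation changes none of symptoms, reporting, work status or response, there is no bias. This stands, and it is why the point is that membership can be changed, not that it will be.
- **Later scores may predict better.** Symptoms at 3 or 6 months may identify late problems better than baseline scores. That is a reason to describe them, not to sort a between-arm comparison by them.
- **One secondary analysis is affected.** This also stands.

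A reader might also infer four stronger things that the article does not support:

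- *Treatment duration is known only after randomisation.* Feasibility evaluation, under Statistical analysis, lists it among the baseline parameters. Because enrolment comes a few weeks after first treatment, the final duration may not be known then. That is an ambiguity, not an established error.
- *Only people already back at work can report cognitive problems at work.* The wording suggests it, but the article does not say who completes the checklist, over what recall period, or how non-workers are scored.
- *The subgroup is selected on the primary outcome.* That outcome is a return sustained for at least 4 consecutive weeks, compared at 12 months. Being at work at 3 months is related to it but not the same. How the criteria combine is not given, so the extent of such selection is unknown.
- *The subgroup result would be uninterpretable.* The illustrated shifts are modest and rest on assumed effects. They show that bias is possible, and no more.

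**Conclusion.** The point holds for the criteria measured at 3 and 6 months. As written, the rule yields a between-arm comparison that randomisation no longer protects.

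Under the assumptions shown, a true RR of 1.00 appears as about 0.98 to 0.96 with a 0.2 SD symptom reduction and about 0.94 to 0.90 with 0.5 SD. In this set-up an intervention that eases symptoms looks mildly harmful in the group it is meant to help most. Other set-ups could reverse the direction, and the entanglement with being at work is not quantified.

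The primary intention-to-treat comparison, the sample size (170, or 190 with loss to follow-up) and the age, sex and education subgroups are untouched. The rule should be corrected, but it does not threaten the trial's main conclusion.

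**What to change.** In Statistical analysis, Effectiveness:

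- Define the high-risk subgroup only from information available at or before randomisation: heavy physical work, baseline work ability, and baseline MFI and CES-D scores if these are collected. Fig. 1 is not shown, so their baseline collection is an assumption to confirm.
- Use treatment duration only as planned or known at baseline, and say so.
- Remove the 3- and 6-month criteria, including cognitive problems at work, from the membership rule, and present those values by arm as description.
- Judge whether the intervention is more effective in this group by the treatment-by-subgroup interaction with its 95% CI, not by the effect within the subgroup alone.

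The cost is one paragraph of wording, with no change to sample size and, if the baseline scores exist, no new data collection. The downside is that baseline symptoms may predict late problems somewhat less well. Recruitment was still open when the article appeared, and the change should be made before outcome data are examined.

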### Sample size

On average, we will include cancer patients at 6 weeks or 42 days after diagnosis, and the follow-up time for the primary outcome return to work will be 12 months after inclusion, hence 12 months and 42 days after diagnosis. Earlier studies in our hospital showed that return to work for patients with various cancer types was 64 % at 12 months of follow-up from diagnosis [28]. In addition, earlier studies in our hospital showed that return to work in the first 42 days is around 8 % [28]. Therefore, the return to work for the control group was set at 64 % + 8 % = 72 %. In a study of Nieuwenhuijsen et al. [29], an intervention group of 35 radiotherapy patients received a supportive work-related intervention in a hospital. Time between diagnosis and the end of treatment was a median 42 days. Return to work was measured between the end of treatment and work resumption and was 89 % after 12 months. Therefore, the return to work for the intervention group in our intervention was also set at 89 %.

Based on our earlier studies on consecutive cancer patients, a power analysis indicated that we should include a total of 170 patients with a follow-up of 1 year after inclusion to indicate a difference of 89 % return to work in the intervention group versus a 72 % return-to-work rate in the control group, with a power of 80 % and *p* < 0.05. Accounting for 10 % loss to follow-up, 190 patients should be included.

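### The question whether Cancer@Work works better in certain patients is not tied to a comparison of effects between subgroups, and the high-risk analysis has no comparator

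*Protocol article*

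**What the plan says.** The Effectiveness section fixes the main analysis: "The relative risk and 95 % confidence interval for returning to work at 12 months of follow-up will be calculated", intervention against control. Two subgroup questions follow, both about a difference in effect.

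- **High-risk patients.** The stated aim is to learn whether the intervention works better for those with the greatest need. The analysis is "a planned subgroup analysis for patients with a high risk of not returning to work will be performed". The group is defined by heavy physical work, low work ability at baseline, long treatment, and high fatigue, depression and cognitive problems at work at 3 and 6 months of follow-up.
- **Age, sex and education.** The aim is "to ascertain whether the Cancer@Work intervention is more effective for various subgroups of patients" who may be more or less likely to benefit from self-management. The analysis is "a subgroup analysis will be done for young versus old, male versus female and lower education level versus higher education level".

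The Statistical analysis section names no interaction test, ratio of relative risks or other comparison of effects between subgroups. The Sample size section, planned at 80 % power and the 5 % level, covers the overall comparison only: "89 % return to work in the intervention group versus a 72 % return-to-work rate in the control group".

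**The concern.** Whether an intervention works better in one group than in another is a question about the difference between two effects. An effect estimated inside one group cannot answer it, however precise it is. For the high-risk patients that is all the text describes. For age, sex and education the wording sets two levels against each other but does not say that their effects will be compared.

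The usual way such an unspecified analysis goes wrong is that each level is tested separately and a significant result in one but not in the other is read as a difference. The trial is sized for about 80 % power overall, so half the sample has only about 50 % power. Discordant pairs would then be common even with identical effects, and the trial could report benefit as confined to the young, to one sex or to one education level without evidence for it.

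**Working it through.** **Inputs.** Return to work 72 % (control) and 89 % (intervention), power 80 %, p < 0.05, and 170 evaluable patients (190 with 10 % loss), all from the Sample size section. The effect measure is the relative risk, from the Effectiveness section. Assumptions, because the article gives no figures: two-sided test, 1:1 allocation, factors that split the sample in half unless stated, and factors independent of one another.

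**1. The plan's own figure.** With the mean proportion p̄ = 0.805 and difference d = 0.17:

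n per arm = [1.96·√(2·0.805·0.195) + 0.8416·√(0.72·0.28 + 0.89·0.11)]² / 0.17² = 84.1, rounded up to 85, so 170 in total. This reproduces the stated number. 170/0.9 = 188.9, rounded up to 189, against 190 stated.

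**2. Power inside a half sample.** With 42 per arm and the same 72 % v 89 % in each half, exact enumeration of the Wald test on the log relative risk gives p = 0.488. The normal approximation for a difference in proportions gives 0.507 at 42.5 per arm.

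**3. Chance that exactly one half is significant.**

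| Truth | Formula | Result |
|---|---|---|
| Same effect in both halves | 2p(1−p) = 2·0.488·0.512 | 0.50 |
| Effect in one half, none in the other | p(1−q) + q(1−p) = 0.488·0.956 + 0.044·0.512 | 0.49 |
| No effect in either half | 2q(1−q) = 2·0.044·0.956 | 0.085 |

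Here q = 0.044 is the exact rejection rate at 42 per arm when both arms are at 72 %. A simulation of 20,000 trials gave 0.50 for the first row and 0.087 for the third.

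With a 2:1 split, power is 0.335 (28 per arm) and 0.627 (57 per arm), and discordance under a common effect is 0.335·0.373 + 0.627·0.665 = 0.54.

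**4. Three factors together.** By simulation with independent factors, at least one discordant pair occurs in about 75 % of trials under the common effect (78 % with 40/60 splits) and about 19 % with no effect.

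**5. The interaction test.** Under the common effect it signals a difference falsely in about 4.6 % of trials per factor, and in about 13 % for any of three, unadjusted. Its power when the full effect is in one half and none in the other (42.5 per arm per half):

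- Log ratio of relative risks: ln(0.89/0.72) = 0.212.
- Variance: 0.11/(0.89·42.5) + 3·0.28/(0.72·42.5) = 0.0029 + 0.0275 = 0.0304, so SE = 0.174.
- Power: Φ(0.212/0.174 − 1.96) = Φ(−0.74) = 0.23.

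The same formula needs about 900 patients (902) for 80 % power.

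**The case against.** A reader might infer that the plan will test each subgroup separately and compare p-values. The text does not say so. Subgroup analysis is a general term that includes an interaction test, setting young against old is comparative wording, the stated output is a relative risk with a confidence interval, and an analysis plan that is not shown may specify the interaction. This stands. It makes the point for age, sex and education one of unclear wording, and makes the 50 % and 75 % figures conditional on a reading rule that the article does not contain. It does not cover the high-risk question, where the text describes an analysis of that group alone.

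A reader might also infer that chance findings would decide who is offered the intervention. The documents do not support that: the abstract and the Discussion tie implementation to the intervention being proven effective and do not mention restricting it to subgroups.

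Two further objections hold. Discordance is far rarer if there is no effect at all. And an interaction term would not rescue the high-risk analysis as defined, because measures at 3 and 6 months come after randomisation and may be changed by the intervention.

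Low interaction power is a fair warning but no reason to leave the question open. It shows how little 170 patients can say about differences in effect.

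**Conclusion.** The point holds in limited form. For the high-risk group, the analysis as written cannot answer the question asked, because it has no comparator and because the group is defined partly by measures after randomisation. For age, sex and education, the text does not say how a difference in effect will be judged.

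If significance were compared between subgroups, a discordant pair would be about as likely when the effect is the same in both halves (50 %) as when it exists in only one (49 %), so it would carry almost no information about who benefits. These figures assume the planning rates, 170 evaluable patients and half splits. The figure for three factors also assumes independent factors. With no effect, discordance is about 8 to 9 % per factor. The overall relative risk, the primary result, is not affected.

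**What to change.** - **Age, sex and education.** State that a difference in effect will be judged by the treatment-by-subgroup interaction, reported as a ratio of relative risks with 95 % CI, for instance from a log-binomial or modified Poisson model with treatment, factor and their product. Show the subgroup relative risks beside it and label all of this exploratory.
- **High-risk patients.** Compare high-risk with other patients in the same way, and define the group only by characteristics measured at or before randomisation. An interaction with a group defined by 3- and 6-month measures is not a valid test of effect modification.
- **Reporting.** Say that significance in one subgroup and not in its counterpart will not be taken as evidence of a difference.

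The cost for age, sex and education is wording only. The high-risk definition must also be reworked around what is recorded at baseline. The downside is low power: about 23 % even for full effect versus none, so most interaction results will be inconclusive. Three unadjusted tests also still carry about a 13 % chance of at least one false signal, which is a further reason for the exploratory label.
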